## Methods/design

### Design

To evaluate the effectiveness of an intervention recently developed for PLH in Botswana, an RCT will be performed. The trial will have two conditions: an intervention group, who will receive the self-help program with coaching for depressive symptoms, and an attention-only control group, who will receive the self-help program without coaching following completion of the follow-up measurement. Random allocation of participants to the intervention or control group will be performed using a stratified random sampling technique. The sample will be stratified according to gender and treatment center. It is important to stratify by gender to ensure approximately equal proportions of males and females in the intervention and control groups. In the study by [name] et al. that investigated intervention targets for depressive symptoms among PLH in Botswana, more females participated compared to males. Additionally, treatment centers are expected to differ with regard to the number of patients included; therefore, stratification will ensure that both the intervention and control groups in large and small treatment centers have almost the same numbers of patients in both conditions.

Random number tables will be used to allocate participants to either condition; these will be computer generated and produced by an independent researcher. Randomization will be done in permuted blocks of six. The independent researcher will enter the numbers into an Excel file which will conceal the randomization until after the participants are established in the trial. The randomization is set up such that the main researcher is unable to see treatment allocation beforehand, minimizing bias. Participants and coaches will not be blinded to allocation to conditions. Participant allocation to one of the conditions will be done after the pre-test.

The study is approved by the Health Research Development Committee of the Ministry of Health in Botswana (Ref. HPDME 13/18/1). The Standard Protocol Items: Recommendations for Interventional Trials (SPIRIT) checklist is provided as Additional file 1.

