### Sample size

To determine the sample size needed for the RCT, we performed a power analysis using the 14th Edition of the Power Analysis and Sample Size Software (PASS) [27]. It was calculated that each group should consist of 64 participants (effect size = 0.50, alpha = 0.05, and power = 0.80). Similar studies have recorded a dropout rate of 15%; therefore, at least 75 participants should be allocated to each group. Taking into account the possibility of further dropout at follow-up, a total of 200 participants will be recruited for the RCT.

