### Statistical analyses

Data will be analyzed using an intention-to-treat (ITT) analysis [43]. We will use a two-tailed alpha of 0.5 for significance testing. To investigate baseline differences between conditions, we will use chi-square and analysis of variance (ANOVA) tests for categorical and continuous variables, respectively.

Differences between groups in depressive symptoms from pre-test to post-tests will be investigated using longitudinal multilevel regression analyses (LMRAs) [44]. We will adopt a two-level model where time and group will be included as fixed effects and the slopes for time and the intercept as random effects. The between-group analysis will include the pre-test, post-test, and follow-up. To investigate the long-term effects of the intervention, we will include the pre-test, post-test, and follow-up in the within-group analysis. To estimate the effects in the model, we will employ a maximum likelihood estimation type. We will also study the differences between participants who followed the intervention to the end and those who dropped out with chi-square tests and ANOVAs.

Furthermore, Cohen’s *d* will be used to calculate within- and between-group effect sizes. Effect sizes less than 0.20 are regarded as having a small effect, 0.50 a medium effect, and 0.80 a large effect [45]. We will also explore clinically significant differences for individual change in depressive symptoms. Individual change scores of 5 or more for the PHQ-9, from pre-test to post-test and follow-up, will be regarded as clinically significant [46]. The same approach will be used to examine pre-treatment versus post-treatment changes with regard to all secondary outcomes.

We will examine moderators of the treatment outcome using LMRA. We will enter potential moderators individually. Additionally, we will employ the latent difference score model for mediation analysis [47].

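### The primary model treats the pre-test only as an outcome and leaves the arms free to differ there; an equal-baseline or baseline-adjusted model would be at least as precise at no cost.

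*Protocol article*

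**What the plan says.** The Statistical analyses section sets out the between-group model: "We will adopt a two-level model where time and group will be included as fixed effects and the slopes for time and the intercept as" (the sentence ends by declaring the last two random). On the time points it adds: "The between-group analysis will include the pre-test, post-test, and follow-up". The stated aim is to compare the arms on depressive symptoms between the pre-test and the later assessments. The section says that the same approach will be applied to the secondary outcomes.

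No baseline score is named as a covariate, and no constraint on the T0 means is mentioned. Baseline severity appears only among the potential moderators (Assessments). The one covariate named for the analysis is referral for intensive treatment, which arises after randomisation (Ethical precautions).

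On timing, the Design section says: "Participant allocation to one of the conditions will be done after the pre-test". The Sample size section says: "It was calculated that each group should consist of 64 participants (effect size = 0.50, alpha = 0.05, and power = 0.80".

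**The concern.** Because randomisation comes after T0, any T0 difference between the arms is chance. A group main effect nevertheless lets the model estimate that difference freely, and information is spent on a quantity that the design fixes at zero. Listing the pre-test as one more time point does not adjust for it. With a free T0 group term, the natural treatment contrast subtracts the whole observed T0 difference, where an adjusted analysis would subtract only the part that the correlation supports.

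At stake is precision on both primary scales (PHQ-9 and CES-D) and on every secondary outcome measured at T0. There is also a question of definition. The model sentence lists no group-by-time term, so the treatment effect itself is left to inference.

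**Working it through.** **Inputs.** From Sample size: d = 0.50, alpha 0.05, power 0.80, 64 per group, 15% dropout, 200 recruited. Sidedness is not stated there; two-sided 0.05 is used. The Statistical analyses section prints a two-tailed alpha of 0.5, which conflicts with 0.05 and is a separate matter. Assumed, because the article does not give them: rho = 0.3, 0.5, 0.7 and k = SD(T0)/SD(T1) = 1 or 0.8. d is on the T1 SD.

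**The plan's own figure.** A two-sided two-sample t-test with d = 0.50 needs 63.8, so 64 per group; power at 64 is 0.801. One-sided testing would need only 50. The stated size therefore matches an unadjusted comparison of two means, with no pre/post correlation used.

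**Variance of the T1 contrast**, in units of the variance of the unadjusted T1 comparison:
- Difference in change (free T0 group term plus group-by-time): 1 + k² − 2·rho·k. With k = 1 this is 2(1 − rho).
- Baseline-adjusted or equal T0 means: 1 − rho².
- Excess of the first over the second: (k − rho)². It is never negative, and is zero only when rho = k.

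With k = 1, generalised least squares on three occasions under compound symmetry gives factors of 1.40, 1.00 and 0.60 (free) against 0.91, 0.75 and 0.51 (equal T0 means) at rho 0.3, 0.5 and 0.7. These match the closed forms. With k = 0.8 the change factor is 1.64 − 1.6·rho, that is 1.16, 0.84 and 0.52.

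**Power (noncentral t).** The 85 per group is 200/2 × 0.85.

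| n per group | k | rho | change | adjusted | gain (points) |
|---|---|---|---|---|---|
| 64 | 1 | 0.3 | 0.66 | 0.84 | 18 |
| 64 | 1 | 0.5 | 0.80 | 0.90 | 10 |
| 64 | 1 | 0.7 | 0.95 | 0.98 | 2 |
| 64 | 0.8 | 0.3 | 0.74 | 0.84 | 10 |
| 64 | 0.8 | 0.5 | 0.87 | 0.90 | 3.5 |
| 64 | 0.8 | 0.7 | 0.97 | 0.98 | under 1 |
| 85 | 1 | 0.3 | 0.78 | 0.93 | 14 |
| 85 | 1 | 0.5 | 0.90 | 0.96 | 6 |
| 85 | 1 | 0.7 | 0.99 | 0.99 | 1 |
| 85 | 0.8 | 0.3 | 0.85 | 0.93 | 7 |
| 85 | 0.8 | 0.5 | 0.94 | 0.96 | 2 |
| 85 | 0.8 | 0.7 | 0.99 | 0.99 | under 1 |

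Gains are taken before rounding the powers. The change contrast is less precise than the unadjusted T1 comparison when 1 + k² − 2·rho·k > 1, that is rho < k/2: below 0.5 for k = 1 and below 0.4 for k = 0.8.

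**The literal model.** With time and group as main effects only, the group coefficient averages the arm differences over T0, T1 and T2. Take true differences of 0, 0.5 and 0.5, equal SDs and compound symmetry. It then estimates (0 + 0.5 + 0.5)/3 = 0.333. At 64 per group its standard error is 0.129, 0.144 and 0.158 at rho 0.3, 0.5 and 0.7, and power is 0.73, 0.64 and 0.56.

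**The case against.** The strongest reply is that the model as printed contains no group-by-time term, so calling the treatment effect a difference in change describes a reconstructed model. This stands. The reading is a fair inference from the stated aim, but it also needs time to be categorical; with linear time the contrast would be a difference in slopes. The literal reading does not rescue the plan, because it dilutes the effect.

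The second reply concerns size. It is tempting to argue that rho will be low because eligibility confines the screening PHQ-9 to 5–19. The same restriction would make the T0 spread narrower than the T1 spread, so k falls below 1 and the gain shrinks. The equal-SD figures at low rho are therefore the least secure. The restriction also acts directly only on the screening PHQ-9, and only indirectly on CES-D.

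Two stronger readings are not supported. A reader might infer that the trial will miss 0.80 power. At 85 per group with equal SDs that happens only at rho of about 0.3 or below, and with k = 0.8 power at rho 0.3 is 0.85. A reader might also infer that regression to the mean passes fully into the estimate. Since T0 precedes allocation, it is equal across arms in expectation and the change contrast is unbiased. Given a chance T0 imbalance with equal SDs, the change score over-corrects by a fraction 1 − rho of it, not by all of it.

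Finally, a mixed model with T0 as an outcome is valid, and covariates are often left to a SAP. But the article itself fixes the time points and fixed effects, so this is a comment on a stated choice, not on an omission.

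**Conclusion.** The point holds as one of efficiency and specification, not of bias. The stated model ignores the equality of the arms at T0 that the design guarantees. Under the change reading it is never more precise than a baseline-adjusted contrast, and is less precise unless rho equals k. Over rho 0.3 to 0.7, the power forgone at 64 per group runs from about 18 down to 2 points with k = 1, and from about 10 to under 1 with k = 0.8. At 85 per group it runs from about 14 to 1, and from about 7 to under 1. These figures rest on assumed rho and k, d = 0.50 on the T1 SD and two-sided 0.05. The loss could be material or negligible, and the article does not let one say which. Under the literal main-effects reading the problem is more basic, since the coefficient is pulled towards the zero difference at T0.

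**What to change.** Amend the model sentence in Statistical analyses. Keep T0, T1 and T2 in the mixed model, with time as categories and group-by-T1 and group-by-T2 terms but no group main effect, so that the T0 means are equal. Alternatively, model T1 and T2 with the T0 score of the same scale as a covariate. Apply this to PHQ-9, CES-D and each secondary outcome measured at T0. Either version also states the treatment contrast explicitly, which removes the dilution under the literal reading.

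The cost is one sentence of analysis wording. The T0 values are already to be collected, no more participants are needed, and according to Trial status recruitment has not started, so the change can be fixed before any outcome is seen.

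### The printed longitudinal model names time and group as fixed effects but no group-by-time term, so its group coefficient averages in the pre-randomisation score and is diluted toward zero

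*Protocol article*

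**What the plan says.** All of this is in the protocol article, mostly under Statistical analyses.

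- Aim: "Differences between groups in depressive symptoms from pre-test to post-tests will be investigated using longitudinal multilevel regression analyses".
- Fixed effects: "We will adopt a two-level model where time and group will be included as fixed effects".
- Random effects: "the slopes for time and the intercept as random effects".
- Occasions: "The between-group analysis will include the pre-test, post-test, and follow-up".
- Estimation: "we will employ a maximum likelihood estimation type".
- Moderators, also to be examined with the longitudinal model: "We will enter potential moderators individually".

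The Design section fixes the order of events: "Participant allocation to one of the conditions will be done after the pre-test". For the main comparison, the article names no group-by-time interaction, no constraint on the pre-test means and no pre-test covariate.

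**The concern.** The aim is a difference in change, but time and group main effects contain no parameter for a difference in change. With the pre-test as an outcome occasion, the only fixed effect that carries treatment is a single group difference assumed equal at T0, T1 and T2. That assumption is false by design if the programme works: at T0 nobody has been allocated, so the expected difference is zero. A steeper decline in the intervention arm has no fixed-effect term of its own and is left to the random slopes.

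At stake is the primary estimate. Reported from the model as printed, it would understate the benefit of the programme, and it would not be the quantity that the aim sentence describes.

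**Working it through.** **1. The plan's own figure.** The Sample size section gives "each group should consist of 64 participants (effect size = 0.50, alpha = 0.05, and power = 0.80". A two-sample t-test at two-sided 0.05 needs 63.77, rounded up to 64, with power 0.801. The figure reproduces, and this point does not affect it. (Statistical analyses prints a different alpha from Sample size. That is a separate matter, and 0.05 is used here.)

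**2. What the group coefficient estimates.** With complete, balanced data and covariance matrix V over the three occasions, the generalised least squares coefficient for a constant group difference is the sum of w_j × d_j. Here d_j is the true difference at occasion j, and w = V⁻¹1 / (1′V⁻¹1).

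Assumed, because the article does not give them: d = (0, 0.5, 0.5) SD and complete data.

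- *Random intercept only.* The weights are 1/3 each at any correlation. Coefficient = (0 + 0.5 + 0.5)/3 = 0.333, which is 67% of 0.50. If the effect halves by T2, it is (0 + 0.5 + 0.25)/3 = 0.25.
- *Random intercept and slope, as planned.* Assume intercept variance 0.5, residual variance 0.5 and visits at weeks 0, 8 and 21 (T2 taken as 13 weeks after T1). For slope SD 0.02, 0.03 and 0.04 per week, the T0 weight is 0.397, 0.453 and 0.507. Coefficient = 0.5 × (1 − T0 weight) = 0.302, 0.273 and 0.246.

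**3. Check by simulation.** 150 trials were simulated with 64 per group, intercept variance 0.5, slope variance 0.05, residual variance 0.45, times 0, 1, 2 and maximum likelihood. The group coefficient of the printed model averaged 0.290 (Monte Carlo SE 0.013); the formula gives 0.288. With group-by-time added, the T1 contrast averaged 0.487 (SE 0.015) against a true 0.50.

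**4. Power.** Random intercept only, unit variance, within-person correlation r, n per group, normal approximation, d = (0, 0.5, 0.5):

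- group term: 0.333 / √[(2/n)(1 + 2r)/3]
- unadjusted T0–T1 change contrast: 0.5 / √[(2/n) × 2(1 − r)]
- baseline-adjusted T1 contrast: 0.5 / √[(2/n)(1 − r²)]

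Power is Φ(ratio − 1.96). At n = 64 and r = 0.5 the ratios are 0.333/0.144, 0.5/0.177 and 0.5/0.153.

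| n = 64 | group term as printed | change contrast at T1 | baseline-adjusted T1 |
|---|---|---|---|
| r = 0.3 | 73% | 67% | 84% |
| r = 0.5 | 64% | 81% | 90% |
| r = 0.7 | 56% | 96% | 98% |

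The plan recruits 200. After its 15% dropout, 200 × 0.85 / 2 = 85 per group remain. The group term then has about 85%, 80%, 76% and 68% power at r = 0.3, 0.4, 0.5 and 0.7. Random slopes lower this: under the step 3 covariance at 64 per group, power is about 50% for the group term and 81% for the T1 contrast.

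**The case against.** The strongest reply is that the sentence is shorthand. It does not say that the list of fixed effects is complete, and it does not name the group main effect as the treatment estimate. The aim sentence describes a difference in change, which in a longitudinal model with random time slopes normally means group-by-time. An article condenses, and a fuller plan may spell the term out. This has force as to intent: the article does not show that its authors mean to test the group main effect. It does not make the printed specification right. The article does not leave the model to another document; it gives fixed effects, random effects, occasions and estimation method, and omits the one term that answers its question.

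A reader might infer that the trial necessarily falls below its stated 80% power. The documents do not support that. With 85 per group and a random intercept only, the group term still reaches about 80% at r = 0.4. At r = 0.3 it beats the unadjusted change contrast, though not the baseline-adjusted one. Neither r nor the slope variance is given.

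A reader might also infer that moderation is not tested at all. That is not supported either. The Background describes the aim as finding out whether some patients benefit more than others, which is effect modification, and entering moderators one at a time does not mean entering them as main effects only.

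Two further points stand. If there is no effect at either later visit, the group coefficient is zero in expectation, so false positives are not inflated. The article also plans between-group Cohen's d and individual PHQ-9 change, so this coefficient is not the only summary of effect.

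**Conclusion.** The concern holds for the model as printed. Its group coefficient includes a difference that is zero by design, so it is biased toward zero and does not estimate the stated aim. Under assumed true differences of 0, 0.5 and 0.5 SD and complete data, one third of the effect is lost with a random intercept only (0.33 SD). With slope SD 0.02 to 0.04 per week, about 40% to 51% is lost (0.30 to 0.25 SD). The direction follows from the order of pre-test and allocation; the size depends on covariances that the article does not give.

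No general loss of power is claimed, because it varies with the correlation, the slope variance and the number analysed. The moderator wording is incomplete rather than shown to be wrong. Because the point concerns the primary estimate, it should be corrected even if the interaction was always intended.

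**What to change.** In Statistical analyses, add group-by-time to the fixed effects with time as a categorical factor, and name the group-by-time contrasts at T1 and T2 as the treatment effect. Preferably constrain the pre-test means to be equal across arms, or use the pre-test as a covariate with T1 and T2 as outcomes (the treatment effect is then the adjusted group difference at each visit). At each correlation tabulated, the baseline-adjusted form has more power than the unadjusted change contrast.

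For moderators, state that the tested term is the moderator-by-group interaction (by time, where the pre-test stays an outcome), with its lower-order terms in the model.

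The cost is a few sentences, with no extra data, visits or participants. Trial status says that recruitment had not started, so the wording can be settled before any outcome is seen.

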**Fig. 1 Fig1:**
[figure not shown]
Flowchart of the study design

In Botswana, the majority of patients who have been on treatment for more than a year visit the treatment center once every 6 months; therefore, the screening will be conducted over a period of approximately 6 months. Any patient who obtains a score > 0 on the PHQ-2 and who meets the inclusion criteria may be referred to the researchers. The HIV consultants will provide written information about the study to the patients and request for permission to provide the researchers with the patient’s contact information (telephone number or email). Following contact with the patients, the researchers will provide further information to the patients and conduct extensive screening for depressive symptoms using the PHQ-9 by telephone. Patients with a score within the mild (> 4) and moderate (< 20) ranges will be eligible for participation in the trial. These patients will then be invited to participate. Those who agree to participate will give consent by a text message to the researchers. Additionally, we will seek permission from patients to inform a medical doctor or general practitioner at the HIV treatment center about their participation in the study. Participants will then undergo a pre-test (T0). Thereafter, the participants will be randomly assigned to the intervention or the control (attention-only) group. The coaches will call all participants at the beginning of the intervention to assess for and stimulate their motivation. This will be accomplished through the use of motivational interviewing and general conversational techniques, providing information about the program, helping the patients plan for the lessons, and advising them to engage in a small activity to get started.

The intervention group will then receive the self-help treatment program with coaching by telephone, while the control group will only receive attention through a weekly telephone chat from a coach. The participants will work on the intervention for 6 weeks (with a maximum extension of 2 weeks). During the intervention, participants will be asked to answer standardized questions at three different times. At 8 weeks, all participants will complete the post-test (T1) and subsequently the follow-up measurement (T2) 3 months later. After the follow-up, participants in the control condition will receive the intervention.

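### The long-term effect is assigned to a within-group analysis, although a randomised comparison at the 3-month follow-up is available and T2 is already in the between-group analysis

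*Protocol article*

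**What the plan says.** The Statistical analyses section of the protocol article opens the efficacy analysis with a comparison of the arms: "Differences between groups in depressive symptoms from pre-test to post-tests will be investigated using longitudinal multilevel regression analyses (LMRAs"). The model has time and group as fixed effects, and a random intercept and random slopes for time. Two sentences then divide the work. The first is "The between-group analysis will include the pre-test, post-test, and follow-up". The second, which is the only one in the section to say how the long-term effect will be investigated, is "To investigate the long-term effects of the intervention, we will include the pre-test, post-test, and follow-up in the within-group analysis". Effect sizes are planned both ways: Cohen's d "will be used to calculate within- and between-group effect sizes".

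The Procedure section fixes the timing: "At 8 weeks, all participants will complete the post-test (T1) and subsequently the follow-up measurement (T2) 3 months later". Until then "the control group will only receive attention through a weekly telephone chat from a coach", and "After the follow-up, participants in the control condition will receive the intervention". The Participants section admits people with a PHQ-9 score above 4 and below 20. The Assessments section names the PHQ-9, with the CES-D, as the measure of the primary outcome.

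**The concern.** A before-after change in one arm does not estimate an effect of the intervention. It is the sum of any program effect, natural recovery over about five months, the effect of regular contact with a coach, any outside treatment after referral, and regression to the mean. The last is plausible here because participants are selected on the PHQ-9, which is then used as an outcome. Randomisation removes these components only when the arms are compared.

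In some waiting-list trials a within-group analysis is all that is left at follow-up, because controls have crossed over. That is not the case here: T2 is measured in everyone before controls get the booklet. Yet the text sends the long-term question to the analysis that lacks this protection. If the intervention arm improved from T0 to T2 but the arms did not differ at T2, nothing in the section says which result answers the question, and its wording favours the within-group one. The article ties implementation in Botswana, and possibly in other countries, to effectiveness, and durability bears on that decision.

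**Working it through.** **1. The plan's own figure.** The Sample size section gives d = 0.50, alpha 0.05, power 0.80 and 64 per group. An exact two-sided two-sample t-test gives 63.77, that is 64, so the figure is reproduced. With 15% dropout, 64/0.85 = 75.3, against the stated 75. Recruitment of 200 gives 100 per arm, and 85 after a 15% loss. The sample size was thus derived for a comparison of two groups, not for change within one.

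**2. Which analyses can use T2.**

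| Analysis | T2 included? | Protected by randomisation? | Role given in the text |
|---|---|---|---|
| Between-group | Yes | Yes | Group differences in depressive symptoms |
| Within-group | Yes | No | Long-term effects of the intervention |

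**3. Illustration of the risk.** Suppose the program has no effect at T2 and symptoms fall by δ SD from T0 to T2 without it. Take equal SDs at both times, correlation ρ, n analysed in the arm, and a paired t-test at two-sided 0.05. The non-centrality is δ√n / √(2(1 − ρ)). At ρ = 0.5 the denominator is 1, so it equals δ√n.

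| n | δ | Non-centrality | Critical t | Significant |
|---|---|---|---|---|
| 64 | 0.2 | 0.2 × 8 = 1.60 | 1.998 | 35% |
| 64 | 0.3 | 0.3 × 8 = 2.40 | 1.998 | 66% |
| 85 | 0.2 | 0.2 × 9.22 = 1.84 | 1.989 | 45% |
| 85 | 0.3 | 0.3 × 9.22 = 2.77 | 1.989 | 78% |

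The between-group contrast at T2 stays at 5% in every row, because both arms share the fall.

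**4. Sensitivity.** With n = 64 and ρ from 0.3 to 0.7, the range is about 27% to 53% for δ = 0.2 and 52% to 86% for δ = 0.3. With n = 85 it is 34% to 65% and 64% to 94%.

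**5. Status of the inputs.** The document gives neither δ nor ρ. Simulating selection on a screening PHQ-9 of 5 to 19 gave regression to the mean between T0 and T2 of 0.14 to 0.25 SD. That assumed a clinic mean of 4 to 6, SD 4.5 to 5, screen–T0 correlation 0.75 to 0.85 and T0–T2 correlation 0.5 to 0.65. Other assumed correlations widened it to about 0.07 to 0.46 SD. The conclusion does not depend on any of these values.

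**6. Power of the alternative.** For d = 0.50 at T2, the two-sample t-test has about 80% power with 64 per arm, 90% with 85 and 94% with 100. A loss of 36% from 100 per arm still leaves 64.

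All calculations use alpha 0.05, as in the Sample size section. The different alpha printed under Statistical analyses is a separate matter.

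**The case against.** The strongest objection is that a randomised analysis including T2 is already planned. The sentence on the between-group analysis comes immediately before the one at issue, between-group d is planned, and the Background and Discussion frame effectiveness as a comparison with the attention-only control. This stands. A reader might infer that natural recovery will be reported as a lasting effect of the program; the document does not support that. It contains no rule that the long-term conclusion rests on within-group significance alone. It also does not confine the within-group analysis to the intervention arm, so an equal fall in controls could be visible. What remains is that the text assigns the long-term question to the wrong one of two planned analyses.

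A reader might also call the control arm untreated at T2. It is better described as not yet given the program. Controls receive six coach calls, and participants in either arm may be referred for treatment and stay in the study.

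The figures are open to challenge too. They rest on assumed inputs, use a paired t-test where the plan has a multilevel model, and the regression-to-the-mean argument is weaker for the CES-D, which is not used for selection. All of this stands, and it is why the percentages are offered only as an illustration.

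Planning a within-group d is not in itself a fault, provided that it is descriptive.

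Finally, a condensed article may leave model detail such as the interaction term to a full analysis plan. That is fair, and its absence is not criticised here. The choice of analysis for the long-term effect is not left out, however; it is stated.

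**Conclusion.** The point holds as a misassigned analysis. The section names within-group change as the way to investigate the long-term effect, when the randomised contrast at T2 exists and is already within the planned between-group analysis. Within-group change could then be presented as a lasting effect without any group difference at T2. Under the stated assumptions (no treatment effect, ρ = 0.5, 64 to 85 analysed, 0.2 to 0.3 SD improvement without the program), the chance of a significant within-arm result is about 35% to 78% instead of 5%. These percentages show how the error works and are not an estimate for this trial. Randomisation, data collection, sample size and the between-group analysis itself are unaffected.

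**What to change.** Replace the sentence on long-term effects with wording such as: *The long-term effect of the intervention is the between-group difference in change from T0 to T2, estimated from the group-by-time term of the between-group LMRA. Within-group changes and within-group Cohen's d will be reported descriptively for both arms, and no claim of effectiveness will be based on them.* State the group-by-time term in the model description, with time coded so that the T2 contrast can be read from it.

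The cost is a sentence or two of text and a slightly fuller model specification. No new data, visits or participants are needed. The Trial status section says that recruitment has not started, so the change can be made before any outcome is seen.
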